**Methods:**

This is a monocentric, open, three-arm randomized controlled trial. The participants are laparoscopically-naive medical students from Heidelberg University. After a standardized introduction to laparoscopic cholecystectomy (LC) with online learning modules, the participants perform a baseline test for basic skills and LC performance on a virtual reality (VR) trainer. A total of 100 students will be randomized into three study arms, in a 2:2:1 ratio. The intervention groups participate individually (Group 1) or in pairs (Group 2) in a standardized and structured multimodality training curriculum. Basic skills are trained on the box and VR trainers. Procedural skills and LC modules are trained on the VR trainer. The control group (Group C) does not receive training between tests. A post-test is performed to reassess basic skills and LC performance on the VR trainer. The performance of a cadaveric porcine LC is then measured as the primary outcome using standardized and validated ratings by blinded experts with the Objective Structured Assessment of Technical Skills. The Global Operative Assessment of Laparoscopic Surgical skills score and the time taken for completion are used as secondary outcome measures as well as the improvement of skills and VR LC performance between baseline and post-test. Cognitive tests and questionnaires are used to identify individual factors that might exert influence on training outcome.

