### Baseline test

After online learning and a VR introduction, all participants take a baseline test at the VR trainer for an initial assessment of basic skills and LC performance. After this test, participants are randomly assigned to one of the three groups.

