### Training curriculum

The curriculum uses multiple training modalities to ascertain several advantages of each, and to give variety to the trainees for ensuring high motivation. In the present study, the multimodality training embraces online learning, box trainers, and VR training. The training groups participate in a standardized and structured multimodality training curriculum involving box and VR trainers either individually (group 1) or in pairs (group 2). Basic skills are trained with the box (Table 1) and VR trainers (Table 2). Procedural skills and complete LCs are practiced on the VR trainer (Table 3). Training in pairs involves less repetitions of each training task per individual participant since pairs are given the same total training time per workplace and must take turns every 30 minutes. The basic and procedural skills exercises of the curriculum are repeated by the training groups during two training sessions of 4 hours until training time is over. The remaining 4-hour training session is used to repeat the LC modules on the VR trainer. The VR trainer permanently records data from exercises including time, precision, economy of motion, instrumental distance, and the number of misaligned clips.

**Table 1 T1:** Box-trainer basic skills exercises

**Nr.**	**Exercise**
1	Moving matches from a box passing them to the other instrument
2	Crossing of 6 rubber bands in a device of 6 screws
3	Cutting out a predefined circle on paper
4	Drawing a rubber band in a device consisting of eyelets and hooks
5	Cutting out a predefined triangle located on a rubber glove
6	Leading needle and thread in the correct order through eyelets screwed on a board
7	Closing a 5 cm cut on foam with a running suture
8	Attaching a simple interrupted stitch on foam

**Table 2 T2:** VR trainer basic skills exercises

**Basic skill**	**Exercise**
Camera manipulation	The 0° and a 30° angled camera is used to locate 10 balls and snap photos of them
Eye-hand coordination	Objects of blue or red colour have to be touched with the respectively colored instrument tips
Clip-application	Ducts have to be clipped to stop the leakage
Clipping/grasping	Leaking ducts need to be safely grasped and then clipped
Two-handed maneuvers	Balls have to be grasped from a jelly mass and placed into a bag with both instruments
Circular cutting	A circular form has to be freed from tissue attachments by cutting with scissors while retracting the form

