### Control group

Group C does not participate in the repetitive training exercises, but is provided the same E-learning, LC introduction, and tests as the training groups. Group C takes the VR baseline test on the first day of the study. The post-test on the VR and POP trainer LC are taken on a separate day.

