### Statistical analysis

The normal distribution provides a fairly exact approximation of the distribution of the scale-specific scores (Figures 1 and two in [46]), which allows standard parametric tests to be used to compare the mean OSATS scores of the three groups [46]. In the first step, overall training effects will be analyzed by a linear mixed model with the main effects Group (1, 2, C), gender (stratification factor), and training pair as a random factor nested in Group 2. If the group effect is not significant at α = 5% in this gatekeeper analysis, statistical inference will stop concluding that there is no substantial training effect at all. If the test is significant, all possible pairs of interventions will be compared (1 vs. C, 2 vs. C, 2 vs. 1) in a similar linear mixed model with group, gender, and training pair (if applicable). These latter analyses will be performed at α = 5% two-tailed, without correction for multiplicity (closed test procedure).

Statistical analysis will be based on the intention-to-treat population that includes all participants that have been randomized and have attended at least one training session. Multiple imputation will be used for missing endpoint information, with linear regression of OSATS scores by the baseline performance on the VR trainer.

Sensitivity analyses will be made using mixed best (Group C) and worst-case (Groups 1 and 2) imputation for the three treatment groups, and vice versa, as well as for the per protocol set of participants that attended all trainings and have complete primary endpoint information.

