### Sample size determination

We plan to examine 40 study participants in the two active arms. This sample size, together with a two-sided α = 0.05, gives 80% power to detect a standardized effect of d = 0.64 with a power of 80%. This effect represents approximately 2.5 points for the general skills scale and approximately 3.5 points for the specific skills scale. As the parameters of the general skills scale range from 1 to 5 and those for the specific skills from 2 to 10, the aforementioned effect would reflect an improvement of exactly one scale unit, which is fairly small. The determination of the sample size for the total scores of general and specific scales can only be estimated, as the correlation between the two scales is unknown. Assuming a positive correlation of *ρ* = 0.5, the standard deviation for the total scores of the scales would be 7.86 for both groups. With the sample size of 40 participants per group and α = 0.05 two-tailed, a difference of 5 points would be detected (for example 3 points for general skills area and 2 points for specific skills area) with a power of 80%. Even smaller differences can be neglected.

In the other analyses, the active study arms are compared with the control group, which consists of students who do not take part in any laparoscopic training. The effect of this control group would be larger than the one of the previous case, thereby allowing for a significantly smaller sample size. In each comparison, a standardized effect of d = 0.79 with 80% power can be measured, which would represent a mean difference of about 6 points on the OSATS scale (for example 3 points for general skills area and 3 points for specific skills area).

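### The intention-to-treat set requires attendance at a training session, which Group C never has; applied as evidently intended, it removes non-starters from Groups 1 and 2 only.

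*Protocol article*

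**What the plan says.** The Statistical analysis section of the protocol article takes as its population the "intention-to-treat population that includes all participants that have been randomized and have attended at least one training session". In the same section Group C is a level of the group factor in the gatekeeper model, one side of two of the three pairwise comparisons, and a named arm in the best- and worst-case imputation.

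Four places say that Group C is not trained. The abstract states: "The control group (Group C) does not receive training between tests". The Control group section states: "Group C does not participate in the repetitive training exercises". The Sample size determination section describes a control group "which consists of students who do not take part in any laparoscopic training". The Randomization section says the same in other words.

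The Training curriculum section uses the term training sessions for the 4-hour blocks of the trained arms. Basic and procedural exercises are "repeated by the training groups during two training sessions of 4 hours until training time is over", and a further 4-hour session is for the cholecystectomy modules. These blocks come after randomisation; the Baseline test section says: "After this test, participants are randomly assigned to one of the three groups".

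The sensitivity analyses include a "per protocol set of participants that attended all trainings and have complete primary endpoint information".

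**The concern.** A condition that one arm cannot meet by design should not define the primary analysis set of a three-arm trial. Taken at its word, the sentence leaves no control arm, and the gatekeeper that opens all further inference loses its third group.

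The natural repair, applying the condition only where training exists, has its own fault. Participants leave Groups 1 and 2 because of something they did after randomisation, and Group C has no matching filter. The trial is open, and the Ethical and legal aspects section lets participants stop at any time, so a student can learn the allocation and not start. If those who do not start would have performed worse, the trained arms look better against Group C than they should.

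The planned imputation handles missing endpoints within the set. It does not bring back people whom the definition has removed. The article describes no analysis of all randomised participants.

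**Working it through.** **1. The plan's own figures.** The article allocates 100 participants 2:2:1, that is 40/40/20. A two-sample noncentral t calculation, two-sided α = 0.05 and ignoring the pairing in Group 2, gives:
- 40 vs. 40, d = 0.64: power 80.7% (stated: 80%).
- 40 vs. 20, d = 0.79: power 81.0% (stated: 80%).

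The stated power therefore assumes that all 40/40/20 are analysed.

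**2. Literal reading.** Group C members with at least one training session: 0 of 20. The set is then at most 40 + 40 + 0 = 80 of 100. The comparisons 1 vs. C and 2 vs. C cannot be estimated, and the gatekeeper reduces to 1 vs. 2.

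**3. Reading applied only to Groups 1 and 2.** Let f be the share of a trained arm that never attends, and s the number of SDs by which these people would have scored lower. The SD of the total score is 7.86 (Sample size determination). The documents give neither f nor s; all values below are assumptions.
- s measured against the attenders: shift = f × s. With f = 0.10 and s = 0.5: 0.10 × 0.5 = 0.05 SD; 0.05 × 7.86 = 0.39 points.
- s measured against the whole arm's mean: shift = f × s / (1 − f). With the same values: 0.05 / 0.90 = 0.056 SD; × 7.86 = 0.44 points.

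Either way the shift is about 0.4 OSATS points. The range under the second formula, with the resulting type I error of a trained arm against 20 controls when training has no effect, is:

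| f | s (SD) | Shift (SD) | Shift (points) | Type I error |
|---|---|---|---|---|
| 5% | 0.5 | 0.026 | 0.2 | 5.1% |
| 10% | 0.5 | 0.056 | 0.4 | 5.4% |
| 10% | 1.0 | 0.111 | 0.9 | 6.8% |
| 20% | 0.5 | 0.125 | 1.0 | 7.2% |
| 20% | 1.0 | 0.250 | 2.0 | 13.8% |

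The table assumes that all controls, including those who would not have started training, are tested. For scale, the plan's detectable difference against C is about 6 points, so 0.4 points is about 7% of it (0.4 / 6).

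**4. The 1 vs. 2 contrast.** The same rule applies to both arms. If f and s are equal in both, the two shifts cancel. Bias needs non-starting to differ between solo and paired training, in frequency or in the kind of person who does not start.

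**The case against.** **The control arm will not actually be dropped.** This stands. A reader might infer from the sentence that Group C would be left out, but the same section plans three analyses with it, and the Objectives section plans to test it. The literal exclusion is a drafting contradiction. The practical risk is the one-sided filter.

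**There is a reading that filters nobody.** The Training curriculum section says that "the multimodality training embraces online learning, box trainers, and VR training", and everyone completes the online learning before randomisation. If that counted as a training session, every randomised participant would qualify, so it would be too strong to say that every alternative reading is harmful. But this reading makes the condition empty. It also fits poorly with that section's own use of training sessions for the 4-hour blocks, and with the statement that controls take part in no laparoscopic training.

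**The per-protocol set does not share the fault.** A reader might infer that it does. It does not: a control with no trainings scheduled can be said to have attended all of them, whereas nobody without sessions can have attended at least one. A per-protocol set also selects on adherence by purpose, and here it is only a sensitivity analysis. What remains is that the wording is ambiguous for Group C.

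**The bias may be small, and imputation may not remove it.** Both parts stand. The shift is assumed, and is small if few fail to start. Controls who do not return also have imputed scores, so they need not contribute observed low values. Imputation from VR baseline corrects only the selection that baseline explains.

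**Conclusion.** The point holds. The stated analysis set contradicts the three-arm analysis in the same section, and this rests on the wording alone, with no assumption. It is a rule stated wrongly, not a detail left to another document.

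Read as evidently intended, the rule drops non-attenders from Groups 1 and 2 only. That is not intention-to-treat and can bias 1 vs. C and 2 vs. C. The size is unknown: about 0.4 OSATS points in the illustrative case, and 0.2 to 2.0 points over the assumed range of 5% to 20% non-starters scoring 0.5 to 1.0 SD below their arm's mean. The documents do not support a claim that the primary 1 vs. 2 contrast is biased; that would need non-starting to differ between those two arms, and nothing in the article shows that it does.

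**What to change.** Define the primary set as all randomised participants, analysed in the arm to which they were randomised, regardless of training attendance. Keep those who never start training eligible for the already planned porcine test where they are willing. Apply the planned multiple imputation and the best- and worst-case analyses to everyone with a missing OSATS score. This is workable because the VR baseline test, which supplies the imputation predictor, precedes randomisation.

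For clarity, state the per-protocol criterion by arm: for Groups 1 and 2, all sessions attended and the endpoint complete; for Group C, no training received and the endpoint complete.

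The cost is a change of wording, a few more imputed outcomes, and possibly a few additional porcine tests of up to 80 minutes each, within the planned 100. Since imputation from VR baseline alone leaves any selection that baseline does not explain, testing willing non-starters is the more useful part of the change.

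### The stated imputation model for missing OSATS scores does not name group, the effect under test; followed as written, it biases the group contrasts, usually towards zero

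*Protocol article*

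**What the plan says.** The Statistical analysis section of the protocol article describes a linear mixed model for OSATS with "main effects Group (1, 2, C), gender (stratification factor), and training pair as a random factor nested in Group 2". It is used first as a gatekeeper test of group and then, if that is significant, for the three pairwise comparisons. VR baseline is not a covariate in this model.

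For missing outcomes the same section states: "Multiple imputation will be used for missing endpoint information, with linear regression of OSATS scores by the baseline performance on the VR trainer". This is the only imputation model given for the main analysis, and VR baseline is its only named predictor. Group, gender and training pair are not mentioned, and nothing says that imputation is done within arms. The Baseline test and Randomization sections place the VR baseline test before allocation.

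On sensitivity the plan reads: "Sensitivity analyses will be made using mixed best (Group C) and worst-case (Groups 1 and 2) imputation for the three treatment groups, and vice versa". A further analysis uses the "per protocol set of participants that attended all trainings and have complete primary endpoint information". No expected rate of missing outcomes is stated.

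**The concern.** An imputation model should contain at least the effects that the analysis model estimates. Here the one named predictor is a pre-randomization score, which randomization balances across arms. The imputed values therefore carry no group effect: a missing control is scored as if partly trained, and a missing trainee as if partly untrained. Repeating the imputation and pooling does not remove this, because every imputation uses the same common line.

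Three features of the trial make it matter:

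- **Missing outcomes are foreseeable.** The Ethical and legal aspects section lets participants stop at any time. For Groups 1 and 2 the porcine LC is on a separate day after training. Controls must return for testing without having been trained, so loss may differ by arm.
- **The sample size has no reserve.** The abstract says: "A total of 100 students will be randomized into three study arms, in a 2:2:1 ratio". That is exactly 40/40/20, and the power statement needs 40 in each active arm.
- **Attenuation is not neutral here.** The Discussion notes that training in pairs would let twice as many trainees take part, so a diluted 1 vs. 2 difference favours a conclusion with practical consequences. A gatekeeper test that fails stops all further inference.

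**Working it through.** **Inputs from the article.** From Sample size determination: 40 per active arm ("We plan to examine 40 study participants in the two active arms", read with the 2:2:1 ratio), SD 7.86 for the total score, a 5-point difference (d = 0.64) for 1 vs. 2, and about 6 points (d = 0.79) for an active arm vs. control. Tests are two-sided at 5%.

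**Assumptions not in the article.** Missing shares of 0 to 30%; data missing completely at random within arm; baseline–OSATS correlation 0.3 (simulation only); arm means of 11/6/0 for Groups 1/2/C, which place the 5-point and 6-point design differences end to end. The resulting 11 points for 1 vs. C is therefore an assumption as well.

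**Step 1: the plan's own power.** Under the normal approximation, power is Φ(d·√(n₁n₂/(n₁+n₂)) − 1.96).

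- d = 0.64, 40 vs. 40: 0.64 × √20 = 2.86, power 81.7% (80.7% with the t distribution).
- d = 5/7.86 = 0.636: 81.2% (80.2% with t).
- d = 0.79, 40 vs. 20: 0.79 × √13.33 = 2.88, power 82.2% (81.0% with t).

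The stated 80% is reproduced.

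**Step 2: expected arm mean when group is omitted.** Baseline is balanced by randomization, so the common line predicts on average the pooled observed mean M:

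`E(mean of arm g) = (1 − f_g)·m_g + f_g·M`, with `M = Σ n_g(1 − f_g)m_g / Σ n_g(1 − f_g)`.

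**Step 3: equal missing shares.** M cancels, and each difference becomes (1 − f) times its true value.

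| Missing in every arm | 1 vs. 2 (true 5) | 2 vs. C (true 6) |
|---|---|---|
| 5% | 0.95 × 5 = 4.75 | 0.95 × 6 = 5.70 |
| 10% | 0.90 × 5 = 4.50 | 0.90 × 6 = 5.40 |
| 20% | 0.80 × 5 = 4.00 | 0.80 × 6 = 4.80 |

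**Step 4: unequal missing shares.**

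- *10/10/30% missing, means 11/6/0.* M = (36×11 + 36×6 + 14×0)/86 = 612/86 = 7.12. Group 2: 0.9×6 + 0.1×7.12 = 6.11. Group C: 0.3×7.12 = 2.13. The 2 vs. C difference is 3.98 instead of 6.
- *20% missing in Group 2 only, means 11/6/0.* M = (40×11 + 32×6 + 20×0)/92 = 632/92 = 6.87. Group 2: 0.8×6 + 0.2×6.87 = 6.17. Then 1 vs. 2 falls to 4.83, 2 vs. C rises from 6.00 to 6.17, and 1 vs. C stays at 11.00.
- *20% missing in Group 2 only, means 6/6/0.* M = (40×6 + 32×6)/92 = 432/92 = 4.70. Group 2: 0.8×6 + 0.2×4.70 = 5.74. A true zero for 1 vs. 2 becomes +0.26.

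**Step 5: simulation of 1 vs. 2.** Design 40/40/20, means 11/6/0, SD 7.86, 10 imputations pooled by Rubin's rules, 1,500 runs, two-sample comparison without a pair effect. The Monte Carlo error of a power near 80% is √(0.8×0.2/1500), about 1 percentage point.

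| Missing in every arm | Estimate, group omitted | Power, group omitted | Estimate, group included | Power, group included |
|---|---|---|---|---|
| 5% | 4.71 | 73% | 4.95 | 78% |
| 10% | 4.52 | 65% | 5.00 | 77% |
| 20% | 4.03 | 48% | 5.00 | 71% |

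With no missing data the simulated power is about 80%. The estimates agree with Step 3. Most of the power lost at 10 and 20% missing comes from omitting group, not from the missing data as such.

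**The case against.** **The article is condensed.** It does not say that VR baseline is the only predictor, and it does not exclude fitting by arm; a reader who infers that by-arm imputation is ruled out goes too far. But the article does state a model and its predictor. On the plain reading group is absent, and a wrong stated rule is not a detail left to the SAP.

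**Not every contrast shrinks.** A reader might infer that all group differences are pulled towards zero in proportion to the missing share. That holds only for non-zero differences with equal shares; Step 4 gives the counterexamples. Nor are imputed scores pulled to one common mean: they are drawn around a common regression line on VR baseline.

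**No inflated false-positive rate was seen.** The +0.26 under a true zero might suggest one. In the simulation with 20% missing in Group 2 only and means 6/6/0, the 1 vs. 2 test rejected in 3.7% of runs with group omitted, so the material does not support that reading.

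**The size is conditional.** With 5% missing the loss is 0.25 points against an SD of 7.86, and three 4-hour sessions may well lose few participants. This stands.

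**Sensitivity analyses are planned.** If data are missing completely at random, the per-protocol analysis of complete endpoints has no imputation bias and could expose the dilution. But it also drops those who missed training, and the best/worst-case analyses only give extreme bounds. Neither corrects the primary result.

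**Adding group is not a cure for everything.** The analysis population includes people who attended a single session. If they supply the missing outcomes, imputing with group credits them with their arm's full training effect. That is a fair caveat, but it does not justify imputing missing controls towards trained scores.

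**Conclusion.** The imputation rule is wrong as written: it leaves out the effect that the primary analysis tests, and it biases the group contrasts even when data are missing completely at random. With equal missing shares, the 5-point design difference loses 0.25, 0.50 or 1.00 points at 5, 10 or 20% missing. Compared with an imputation model that contains group, power for 1 vs. 2 is lower by about 5, 12 or 23 percentage points (78 − 73, 77 − 65, 71 − 48). Unequal shares can do more harm, as in the 10/10/30% case where 2 vs. C falls from 6 to 3.98, or can leave or slightly raise a contrast. Attenuation is the usual direction, not a universal one.

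The closed-form results rest on assumed missing shares and on missingness completely at random within arm. The unequal-share results also rest on the assumed arm means, and the power figures on the 0.3 correlation and the absence of a pair effect. That group is missing from the stated model depends on none of these.

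**What to change.** State in the Statistical analysis section that missing OSATS scores are imputed from a regression containing group, gender and VR baseline, or that imputation is done separately by arm. This takes one sentence, uses variables already collected, needs no further participants, and should be settled before the data are analysed.

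Two refinements are optional. Accounting for training pair in Group 2 would match the random factor in the analysis model, but it needs a partially nested imputation model and so more than a sentence. The VR post-test could serve as an auxiliary variable where it is available.

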## Methods

### Objectives

The primary goal of this study is to examine whether study participants who undergo laparoscopic training individually (group 1) perform better after the training than study participants who undergo the same training in paired teams (group 2). The control group (group C), which does not receive training, exists to assess the importance of training for a successful operative outcome. Baseline and post-tests are performed on the VR trainer (Figure 1). The operative performance in all three groups will be tested on a cadaveric porcine model with the pulsating organ perfusion (POP) trainer at the end of the study and will be evaluated according to standardized and validated assessment criteria by blinded raters [37-40]. Secondary goals include assessing the influence of individual trainee characteristics on surgical training and performance [35,41,42].

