### Blinded test evaluation

The post-test LC with the POP trainer and cadaveric animal organ is used to evaluate and compare the operative performance of all participants. The POP trainer simulates MIS with perfused cadaveric organs. The artery of a hepato-biliary organ can be catheterized and linked to the frequency and pressure controlled POP trainer pump and perfused by colored water. The perfused liquid flows back into the POP trainer via side arms of the arteries, veins, and parenchymal lesions. The Objective Structured Assessment of Technical Skills (OSATS, range 20 to 100) is used as the primary endpoint of the study (Table 4). The expert raters are blinded to the training status of the participants. The OSATS consists of two evaluative spectra and allows for the evaluation of general laparoscopic surgical skills as well as specific procedural and technical skills for the operation. The unweighted sum of the two scales will be evaluated as the primary endpoint.

**Table 4 T4:** Objective structured assessment of technical skills (OSATS) scores

**OSATS**	**Objective structured assessment of technical skills**	**20–100 points**
**GRS**	**General rating scale**	**6–30 points**
	Respect for tissue	1–5 points each
	Time and movement	
	Use and knowledge of instruments	
	Use of camera-assistance	
	Operational duct and anticipation	
	Need of assistance	
**STS**	**Specific technical skills scale**	**14–70 points**
	Retraction of the gallbladder and exposition of Calot’s triangle	1–5 points each
	Preparation of the cystic duct	
	Clipping and sectioning of the cystic duct	
	Preparation of the cystic artery	
	Preparation of the liver bed	
	Specific knowledge about operational techniques	
	Overall quality of the operation	

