### Ethical and legal aspects

All data for the study are recorded anonymously, treated confidentially, and are evaluated by authorized staff for scientific purposes only. Participants’ names are kept separate from all study data and are not used for the study. Each participant is assigned a designated code that is used for the entire study documentation and data collection. The study courses are offered in addition to compulsory university courses. Participation in the study is voluntary and may be ended at any time. There are no foreseeable negative consequences for participants related to participation. The participating staff of the Heidelberg MIS center is experienced in the handling of training devices and in tutoring MIS. The benefits of training for students are numerous: stamina, concentration, and manual adroitness are enhanced and practiced, surgical interest may be stimulated or invigorated, and students are able to begin their first practical laparoscopic experience, which may be used during later work. In the event that a participant’s physical or mental health becomes jeopardized due to participation in the present study, the participant will be dismissed immediately and excluded from the study. Ethical approval was obtained by the local ethics committee at Heidelberg University prior to the beginning of the study (Code S-334/2011). Written informed consent is obtained from each trainee.

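### The two extreme-case imputation runs shift Groups 1 and 2 the same way, so they do not bound the primary solo-versus-pair difference when both arms lose OSATS scores

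*Protocol article*

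**What the plan says.** Under Objectives, the protocol article makes solo against paired training the main question: "The primary goal of this study is to examine whether study participants who undergo laparoscopic training individually (group 1) perform better after the training", compared with those who train in pairs. Group C is there to show whether training matters at all. The primary endpoint is fixed under Blinded test evaluation: "The Objective Structured Assessment of Technical Skills (OSATS, range 20 to 100) is used as the primary endpoint of the study".

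The Statistical analysis section sets out the testing order. An overall group test acts as gatekeeper, and then: "If the test is significant, all possible pairs of interventions will be compared (1 vs. C, 2 vs. C, 2 vs. 1").

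The same section handles missing scores in three ways:

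- Main analysis: "Multiple imputation will be used for missing endpoint information, with linear regression of OSATS scores by the baseline performance on the VR trainer".
- Extreme-case sensitivity analysis: "mixed best (Group C) and worst-case (Groups 1 and 2) imputation for the three treatment groups, and vice versa".
- Per-protocol sensitivity analysis, on the "per protocol set of participants that attended all trainings and have complete primary endpoint information".

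Loss of endpoint data is possible. Ethical and legal aspects states: "Participation in the study is voluntary and may be ended at any time". No expected loss rate is given.

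**The concern.** On its plain reading, the extreme-case rule defines two runs: Group C best with Groups 1 and 2 worst, and Group C worst with Groups 1 and 2 best. This pits the trained arms against control. It never pits Group 1 against Group 2, which is the contrast the trial was set up and sized to answer.

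A best/worst-case analysis bounds a difference only if the two arms being compared are pushed in opposite directions. If both are pushed the same way, most or all of the shift cancels in the difference. A reader who sees two almost equal estimates of the solo-versus-pair effect could conclude that it is insensitive to missing data, when the agreement comes from how the runs were built.

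Nothing else in the section fills the gap. The multiple imputation is the main analysis, not a stress test. The per-protocol set drops participants without a score, so it varies no missing value. Rerunning the gatekeeper under the extreme cases would show whether the Group 2 versus Group 1 test is reached, not how far its estimate could move.

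**Working it through.** **Inputs from the protocol article**

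- n = 40 per training arm, SD 7.86 for the total score, difference of 5 points (Sample size determination).
- OSATS range 20 to 100 (Blinded test evaluation).

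**Assumptions**

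- An observed difference of 5 among those with scores.
- The numbers missing, k1 in Group 1 and k2 in Group 2.
- Worst and best values, W and B, common to both arms. The article does not define them, so three choices are shown: 1 SD either side of the pooled mean (B − W = 15.72), 2 SD either side (31.44), and the scale limits (80).

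**The plan's own figure.** With 40 per arm and d = 5/7.86 = 0.636, two-sided α = 0.05, power from the noncentral t distribution is 0.802. The stated 80% is reproduced, and this point does not affect it.

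**Formula.** After imputation each arm mean is ((40 − k) × observed mean + k × imputed value)/40.

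*Equal losses, k in each arm*

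- Planned runs (both W or both B): the imputed terms cancel, leaving (40 − k)/40 × 5. For k = 2 this is 38/40 × 5 = 4.75; for k = 4 it is 36/40 × 5 = 4.50. Both runs give the same number, whatever W, B and the observed means are.
- Opposed runs: the same quantity −/+ k/40 × (B − W).

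| Missing | Planned (both runs) | Opposed, 1 SD | Opposed, 2 SD | Opposed, limits 20 and 100 |
|---|---|---|---|---|
| 2 + 2 | 4.75 | 4.75 ∓ 0.79: 3.96 to 5.54 | 4.75 ∓ 1.57: 3.18 to 6.32 | 4.75 ∓ 4.00: 0.75 to 8.75 |
| 4 + 4 | 4.50 | 4.50 ∓ 1.57: 2.93 to 6.07 | 4.50 ∓ 3.14: 1.36 to 7.64 | 4.50 ∓ 8.00: −3.50 to 12.50 |

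*Unequal losses, values at 2 SD.* With the observed means 2.5 either side of the pooled mean, the observed part is 2.5 × (80 − k1 − k2)/40. The imputed part is ∓15.72 × (k1 − k2)/40 in the planned runs and ∓15.72 × (k1 + k2)/40 in the opposed runs.

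| Missing (Group 1, Group 2) | Planned | Opposed |
|---|---|---|
| 3, 1 | 4.75 ∓ 0.79: 3.96 and 5.54 | 4.75 ∓ 1.57: 3.18 and 6.32 |
| 4, 2 | 4.625 ∓ 0.786: 3.84 and 5.41 | 4.625 ∓ 2.358: 2.27 and 6.98 |
| 4, 0 | 4.75 ∓ 1.57: 3.18 and 6.32 | identical |

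**Effect on the test.** These p-values come from two-sample t-tests with 78 df, with the variance recomputed to include the imputed values. Pair clustering and gender are ignored.

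- 2 + 2 at 1 SD: adverse opposed run 3.96, p = 0.029.
- 2 + 2 at 2 SD: planned p = 0.014 in both runs; adverse opposed run p = 0.10.
- 4 + 4 at 1 SD: planned p = 0.012; adverse opposed run p = 0.11.
- 4 + 4 at 2 SD: planned p = 0.026; adverse opposed run p = 0.52.
- 4 and 2 at 2 SD: planned p = 0.053 and 0.006; adverse opposed run p = 0.26.
- 2 + 2 at the scale limits, assuming observed means of 60 and 55: planned p = 0.064 and 0.084; adverse opposed run 0.75, p = 0.78. The planned p-values rise only because the extreme values inflate the standard error, from 1.76 with complete data to 2.52 and 2.71. The estimate stays at 4.75.

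**The case against.** The strongest reply is that the plan labels these runs sensitivity analyses and never claims that they bound the Group 2 versus Group 1 difference. They also suit the gatekeeper: if the overall group effect fails, inference stops, so stressing the trained arms against control tests whether the main comparison is reached. The article is a condensed account, and further scenarios could sit in an analysis plan that is not shown. All of this limits the weight of the point, since the primary analysis itself is not in error. It does not remove the point, because the article names the specific scenarios and they do not fit its own primary contrast.

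The harm is also conditional:

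- False reassurance is most likely with similar losses in both arms and imputed values short of the scale limits. At the limits, 2 + 2 missing already costs the planned runs their significance. With unequal losses the planned runs visibly separate.
- Small losses with mild values change nothing. At 1 SD with 2 + 2 missing, or at 2 SD with 1 + 1 missing (adverse opposed p = 0.030), the result stays significant.
- Exact equality of the planned estimates needs imputed values common to both arms. Arm-specific extremes could separate the runs, though they would still not be bounds.

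These limits stand. Finally, a delta or tipping-point analysis would serve as well as opposed extremes. That is a fair choice for the trial team, but some analysis that moves the two arms apart is still needed.

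**Conclusion.** The concern holds. Both stated extreme-case runs put Groups 1 and 2 on the same side, and no other stated analysis moves them in opposite directions. With equal losses and common imputed values, the gap between the planned estimates is zero, while the true bounds are 2 × k/40 × (B − W) apart: 3.14 points for 2 + 2 missing at 2 SD, and 8 points at the scale limits. With unequal losses the planned runs are a partial test. With losses in one training arm only, they are complete.

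The cancellation does not depend on the observed means or on the values chosen, provided the values are shared. The practical size does depend on the loss counts and imputed values, which are assumptions because the documents give neither. With no losses there is no effect. The weakness lies in the sensitivity analysis of the primary comparison; the main analysis and the sample size are untouched. It should be corrected because it concerns the trial's main question and the correction is cheap.

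**What to change.** Keep the two planned runs for the comparisons of Groups 1 and 2 with Group C. For Group 1 versus Group 2, add two runs of the same model: missing OSATS scores worst in Group 1 and best in Group 2, and the reverse. State that these two are to be read as bounds on the solo-versus-pair difference, and that agreement between the planned runs is not evidence of robustness for that comparison.

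The cost is two further model runs and one sentence in the Statistical analysis section. The drawback is that the bounds are pessimistic, and wide if the scale limits are imputed (−3.50 to 12.50 with 4 missing per arm in the example), so they should not be presented as likely results.
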